### Dosage of medicines to be used

Infants randomised to the intervention arm will receive the first dose of antibiotics in the outpatient department. Those randomised to the control arm will be hospitalised and receive injectable antibiotics (**Table 4**).

**Table 4 T4:** Treatment arms

	Hospital arm		Outpatient arm	
	Injection Gentamicin	Injection Ampicillin	Injection Gentamicin	Oral Amoxicillin
Route	IM	IM / IV	IM	Oral
Frequency (per day)	Once	Two to Four*	Once	Twice
Dose by weight	Strength, 40 mg / ml	Strength 250 mg / 1.5 ml	Strength, 40 mg / ml	250 mg Dispersible tablet
1.5-2.4	0.2	0.8	0.2	1 / 2 tablet
2.5-3.9	0.4	1.2	0.4	1 / 2 tablet
4.0-5.9	0.6	1.5	0.6	1 tablet

IM – intramuscular, IV – intravenous, mg – milligramme, ml – millilitre

*Depending on the age of the child, for the hospitalised child, twice daily in the first week of life, thrice daily in 2-4 weeks of life, four times daily in 4+ weeks of life [4].

### Treatment documentation

The study treatment documentation and compliance team will document the treatment received in the hospital (control) and home (intervention) from days one to seven after enrolment. For infants in the control arm, the documentation of treatment received will be captured from the hospital inpatient treatment charts. For infants in the intervention arm, the documentation of treatment received will be captured in the OPD physician notes or reported by the mother.

### Study outcomes

The poor clinical outcome will be defined as: 1) death at any time from randomisation up to day 15 of initiation of therapy, or any sign of critical illness (no movement at all, unable to feed at all, or convulsions) on day 2, 4 or day 8 post-randomisation, or 2) any sign suggestive of another serious infection, e.g., meningitis, bone or joint infection on day 2, 4 or day 8 post-randomisation, or 3) any new CSI sign on day 4 or day 8 post-randomisation, or 4) persistence of the presenting CSI sign on day 8 post-randomisation.

### Outcome assessment

The proposed trial cannot be blinded due to the nature of the treatment. It is, therefore, important to incorporate measures to reduce potential measurement bias in the design of the study. We will use independent outcome assessors (IOA), who will be trained nurses or physicians or clinical field workers and will be independent of the enrolment and treatment to evaluate study outcomes. IOAs will be trained in standard management and study procedures. Outcome assessment will be carried out by independent outcome assessors (IOAs) and members of the outcome assessment team, who will visit all enrolled young infants on days 2, 4, 8 and 15 after enrolment. In the hospital arm, the outcome visits on days 2 and 4 will be done in the hospital, while the days 8 and 15 visits will be done at home (or in the hospital or where ever the child may have moved to). In the outpatient arm, the outcome visit on day 2 will be done when the infant returns to the hospital to receive the day 2 gentamicin injection. The outcome visits on days 4, 8, and 15 will be done at home or where ever the infant may have moved to.

The IOAs will only ascertain outcomes per the criteria mentioned above under outcomes. A case will be considered a poor clinical outcome if the IOA confirms it.

### Follow-up

All infants will be followed up till day 15 after initiation of therapy. Infants in the intervention (outpatient) arm will be asked to return to the hospital for treatment and assessment by the hospital physician / nurse on days 2 and 4 of treatment initiation. Infants will be assessed for the presence of any adverse event during scheduled follow-up visits to the hospital OPD, hospital visits by the family for care-seeking at any time during the follow-up period, or reported to the IOA team during a home visit and referred for care. These will be managed by the treating physician as per routine practice and followed up till resolution.

Infants in the inpatient arm will be followed up and managed as per routine hospital procedures.

All efforts will be made to follow all the enrolled young infants in the study. In case a young infant does not come to the hospital / health facility on the day of follow-up, the study team will contact them by phone and counsel parents/caregivers to bring the infant to the hospital / health facility. Transportation or transportation costs will be provided to families so that it is not a burden on the family to come for follow-up.

### Data handling and confidentiality

Data will be collected prospectively using electronic devices. Protecting the confidentiality of the data collected in the study will be a high priority. The consent form and any other forms linking participant personal information to study ID numbers will be kept in securely locked filing cabinets. Regular backups of the existing data will be done at appropriate intervals. All computers being used in the study will be password protected and will have restricted access to specific study staff to protect confidentiality. Participants’ names or identifiers will not be used in any publication. The paper-based log books will be kept for 10 years from the date of screening to complete all analyses, and then these will be destroyed.

### Data management

All study data will be collected on electronic case report form (CRF). Each site will collect data using Android-enabled devices using the PSBI data management system developed on the Tangerine software platform (http://www.tangerinecentral.org/ and https://docs.tangerinecentral.org/). Quality control will be performed on-site: each research team member will be responsible for data quality checks and ensuring that all forms are correctly filled out. A central data repository will be created. All efforts will be made to minimise missing data. There will be no imputation of missing data. RTI will develop and support a common data management system in collaboration with WHO and site investigators, conduct statistical analysis and support data monitoring, and perform on-site monitoring visits to improve the quality of data. Standardised data collection tools will facilitate the study data to be entered directly into the electronic forms using laptops, notebooks, or other portable electronic equipment. While centralised, however, each site will also own and support the data collection system. The data management system will be maintained and managed locally at each site, with support, as needed, from RTI technical staff. RTI will develop a data monitoring plan in collaboration with the WHO and study investigators to provide regular reporting on data recruitment, adherence to the study protocol and other metrics deemed important. RTI will provide periodic additional reports as needed (i.e., in preparation for the DSMB or Steering Committee meetings) from the centralised monitoring.

### Data analysis

Means and proportions of baseline characteristics by inpatient and outpatient groups will be presented. The primary analyses will be intention-to-treat to compare the risk of poor clinical outcomes between the intervention and control arms. Risk difference and the 95% confidence intervals will be presented to assess. Those who will be lost to follow-up and from whom consent would be withdrawn will not be included in the per-protocol analysis. The treatment outcomes between control and intervention groups will be compared, and the difference in the risk of poor clinical outcomes together with 95% confidence intervals, will be calculated. Secondary analyses will be performed to investigate the effect on secondary outcomes (predictors of poor outcomes); that is, univariate and multivariate regression analyses will be performed to identify predictors of poor clinical outcomes.

### Quality control and assurance

All study teams (screening, enrolment, and outcome assessment teams) will have study supervisors who will support adherence to the manual of operations. The quality assurance team will conduct regular standardisation exercises, oversight and monitoring of all study activities through regular and random visits and checks of proportion (10%) of all completed study forms. A site preparation review will be conducted before the initiation of the study. This will include the standardisation of practices and measurements. WHO staff and study consultants will provide external oversight and support to ensure the quality of study implementation.

### Quality of care in hospitals

The hospital infant care services will be strengthened regarding human resources and capacity building through training, processes and standard operating procedures (SOPs), ensuring continuous availability of standard quality antibiotics and basic support for routine care. The “minimum” quality of care will be according to the WHO pocketbook for hospital care for children [4], which includes keeping the baby warm and providing kangaroo mother care to prevent hypothermia (in those who need it), encouraging a mother to breastfeed frequently to prevent hypoglycaemia, fluid management when required, basic laboratory support, and oxygen therapy when needed [4]. The hospital team will be oriented on the study protocol and recommended treatment protocols, including information on indications for changing the treatment regime. Regular visits to assess the quality of care at the hospitals will be made by an experienced paediatrician / neonatologist. Medical equipment provided to the participating hospitals for the study will remain there after the completion of the study.

### Training of health workers and study staff

The study staff who will perform screening, enrolment, and outcome measurement will be trained using standardised study SOPs. Data will be collected by research staff on standardised data collection forms. During training, emphasis will be placed on maintaining Good Clinical Practice (GCP) standards. All research staff will be trained in rapport-building and communication with mothers / caregivers. The screening and enrolment study staff will be trained in introducing the study to potential participants, administering the consent form, assessing for clinical signs and eligibility, and completing all relevant study forms. The outcome measurement staff will be trained in the definitions of outcomes and on their standardised assessment, as well as completion of the outcome assessment forms.

### Standardisation and refresher training

Periodic standardisation exercises every quarter will be carried out for study staff, supervisors, and IOAs to identify clinical signs to maintain their clinical skills. The study sites will also develop a system of periodic refresher training for health workers, supervisors and IOAs through clinical practice and / or video demonstrations. In addition, periodic centralised standardisation exercises and refresher training will also be conducted by WHO for the study staff.

### Logistics and commodities

All sites will be equipped with necessary medicines, equipment and logistics for pneumonia case management, such as ampicillin and gentamicin injections, oral amoxicillin 250 (or 125) mg dispersible tablet, pulse oximeter with accessories, digital and mercury thermometers, digital weighing scales, respiratory rate counting timers / digital timers and other necessary materials centrally through the WHO supply division to maintain standardisation. The study teams will monitor the equipment for periodic standardisation and replacement of faulty devices, if any. The consumables will be replenished as per need.

### Supervision

All study staff will be supervised by a study supervisor. All young infants who are assessed as potential enrolment will be periodically validated by a supervisor to ensure quality. Supervised accompanied visits and independent unaccompanied visits will be carried out regularly by the supervisors. Video calls or video clips of signs, eg, chest indrawing, will also be used in real-time to allow supervisors to monitor the correct identification of signs from time to time. Principal investigators and co-investigators will also make random visits to check the project's performance and quality.

Periodic meetings of the research implementation teams will be held to review enrolment, performance, observations and follow-up problems and identify solutions / required actions to overcome those. Action points will be followed up on in the next meeting.

### Monitoring

Monthly progress reports will be submitted by all the sites to the coordinating site at the WHO, which will be reviewed, and feedback will be provided. Regular conference calls will be held with all sites to discuss the progress and critical issues of the study. Databased monitoring, as well as verification of serious adverse event (SAE) forms, will be carried out by the DCC in collaboration with the WHO study coordination team. Investigators and study coordinators will randomly visit the field sites to observe study staff, supervisors and IOAs performing their activities. They will cross-check a small proportion of collected CRFs and share observations with supervisors and IOAs.

### External monitoring

The WHO study coordinating team will visit each site before the initiation of the study to assist in the preparation and planning of the site implementation of the protocol and study procedures. Due to restrictions on travel because of the COVID-19 pandemic, virtual visits and the monthly online meeting will be held. Country-based or other external WHO monitors will visit each site at least once or twice a year to monitor the progress and observe the procedures using a checklist to monitor clinical trials. It will include assessment and enrolment procedures, clinical practices such as counting respiratory rate, identifying danger signs, conducting pulse oximetry, and review other study procedures, and data management. Various logbooks will be checked. A proportion of completed electronic CRFs will be checked, and all SAE reporting forms will be reviewed. WHO monitors will also observe physician awareness and will meet with the regular hospital staff. In addition, they will make a home visit to those who are receiving treatment in the intervention group and talk with the parents. When possible, the monitors will meet with the community groups’ members, ministry and district health officers, and programme managers at different levels. Recommendations arising from the site monitoring visits will be shared and discussed with the principal investigators and other project staff at the site office, and follow-up actions will be undertaken.

### Ethical considerations

The protocol has been approved by all the local institutional ethical review committees at the study sites and the WHO ethical review committee. Where required, national and regional / state approvals have been obtained. The safety of enrolled infants in this trial will be ensured by close monitoring and follow-up. The trial will follow CIOMS and Good Clinical Practice guidelines.

### Informed consent

Informed written consent will be obtained from parents / caregivers by a study nurse / physician at two stages, first at the time of screening and later at the time of enrolment. Detailed verbal communication in the caregivers’ native language will be provided to ensure comprehension of the trial and study procedures. If the participant is illiterate, then a witness signature will be required. All consent forms will be translated into local languages. Parents / caregivers of sick young infants will be provided basic information about the study and invited to consent for the screening. Parents/caregivers of infants found to be eligible after the screening will be provided full information about the study and invited to have their infant participate in the study. The eligible infants will be enrolled if their parents / caregivers provide informed consent and will be randomised to either one of the treatment arms. Illiterate parents / caregivers will be asked to give a thumbprint on the consent form; literate parents/caregivers will be requested to sign the consent form. Study staff will be trained in the study methodology, including obtaining consent.

### Patient safety

The study procedures and data collection will not pose any significant physical, psychological, social, legal or other kinds of risks to the participants. Clinical assessment and illness management, including the provision of drugs to be used in this study, are routinely used in clinical practice. Every enrolled subject will be followed up till the completion of treatment and assessed on day 15 of the enrolment. Treatment failures will receive an appropriate change of antibiotic therapy according to standard clinical practice, and those who need hospitalisation will be referred and admitted to the sub-district / district / tertiary care hospitals immediately for appropriate management, as required. Other discomforts to caregivers might include a longer waiting time for data collection. However, the procedures will be explained in detail, and any queries by parents will be answered. The mobile phone number of the responsible study staff and study supervisors will be provided to all participants’ caregivers so that they could reach them if needed.

We will counsel and empower the mother / caregivers / families at enrolment and on all follow-up visits to 1) recognise danger signs or signs of illness and seek care and 2) know when to return to the hospital for follow-up care. We will train the mother / caregiver / family on the quantity, frequency and process of giving oral antibiotics at home. Systems will be in place in the hospital to provide emergency and rescue care in case of any adverse event or facilitate referral to a higher facility if required.

### Adverse events – documentation, reporting and response

Any adverse event that occurs after enrolment will be recorded on an adverse event reporting form by the treating nurse / physician. In case of an SAE, the study staff will contact the study supervisor and IOA. The IOA will document the SAE and convey the information to the study coordinator / investigator. An SAE, like death, anaphylactic reaction, severe diarrhoea, and a disseminated or severe rash, will be reported to WHO within 48 hours of the occurrence. These cases will be (except the ones who unfortunately die) referred for appropriate treatment and will be followed up. In case of other minor adverse effects, such as mild rash etc., the treatment will be continued. WHO will report SAEs to the Data Safety Monitoring Board (DSMB).

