### Control

Inpatient antibiotic treatment initiated with WHO recommended antibiotic regimen – injectable ampicillin (twice or thrice a day, depending on age) plus injectable gentamicin (once daily) along with other supportive care for 7-10 days.

One of the possible reasons that outpatient care was observed to be better than hospital care in previous studies might be the poor quality of care in hospitals. In this study, we would like to reduce this factor as far as practically feasible. This means that the quality of care at the study hospitals will be reviewed against the WHO pocketbook for hospital care for children [4] and will be improved using quality improvement approaches to ensure a “minimum” quality of hospital care. Efforts to improve the quality of care will also be made at outpatient facilities.

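### During treatment, non-serious adverse events are recorded by treating staff whose scheduled contact differs by arm, and the outcome assessor, who could even this out, has a contradictory safety role

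*Protocol article*

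**What the plan says.** All references are to the protocol article.

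- **Who records.** The section on adverse events states: "Any adverse event that occurs after enrolment will be recorded on an adverse event reporting form by the treating nurse / physician". It also has the independent outcome assessor (IOA) document serious adverse events (SAEs), and each SAE "will be reported to WHO within 48 hours of the occurrence".
- **Outpatient contact.** Under Follow-up, outpatient infants are asked to "return to the hospital for treatment and assessment by the hospital physician / nurse on days 2 and 4 of treatment initiation". The first dose is given in the outpatient department on day 1 (Dosage of medicines to be used). Adverse events may also be picked up through "hospital visits by the family for care-seeking at any time during the follow-up period, or reported to the IOA team during a home visit".
- **Inpatient contact.** Under Follow-up: "Infants in the inpatient arm will be followed up and managed as per routine hospital procedures". No adverse-event schedule is stated for this arm. Treatment is "plus injectable gentamicin (once daily) along with other supportive care for 7-10 days" (Control), with ampicillin given "twice daily in the first week of life, thrice daily in 2-4 weeks of life, four times daily in 4+ weeks of life" (Table 4 footnote).
- **Assessors.** They visit both arms on days 2, 4, 8 and 15 (Outcome assessment). The same section says: "The IOAs will only ascertain outcomes per the criteria mentioned above under outcomes". Box 2, however, gives the assessment team the SAE case report form.

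**The concern.** The arms differ in where the infant is, and so in how often the person responsible for recording adverse events sees the infant. That person also knows the allocation. If a transient rash or loose stools on day 5 or 6 is noted on the ward but not at home, the arms can show different counts at the same true rate. The direction would favour outpatient care.

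The protocol recognises the general problem. Because blinding is impossible, it introduces independent assessors to limit measurement bias in the outcome. The article does not say that they ask about adverse events in the same way, and one sentence, read literally, tells them not to.

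What is at stake is the tolerability half of the trial's message. The abstract's Discussion and the Conclusions both aim at a statement that outpatient treatment is safe as well as effective. A count of non-serious events that depends on intensity of observation would be weak support for it.

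**Working it through.** **No figure to reproduce.** The protocol gives no adverse-event rate, detection rate or planned adverse-event comparison. The check consists of counting contacts, setting the statements on the assessor's role side by side, and one illustration on assumed inputs.

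**1. Scheduled treating-staff days, days 1 to 7**

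- Inpatient: gentamicin once daily and ampicillin at least twice daily imply contact on every day, so 7 days. This is inferred; the text says only that routine procedures apply. The treatment length is seven days in the abstract and the research question but 7-10 days under Control. Ampicillin is twice or thrice daily under Control but two to four times in Table 4. These statements need reconciling, but the count of 7 holds under any of them.
- Outpatient: days 1, 2 and 4, so 3 days. Days without scheduled treating-staff contact: 7 − 3 = 4 (days 3, 5, 6 and 7).

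Adding assessor visits on days 2, 4, 8 and 15:

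- Inpatient contact days: 1 to 8, and 15.
- Outpatient contact days: 1, 2, 4, 8 and 15.

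With a seven-day stay, the difference lies entirely in days 3, 5, 6 and 7. A stay of up to 10 days would extend it slightly. After discharge both arms depend on the same assessor visits plus care-seeking.

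**2. The assessor's role**

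| Section | Role stated |
|---|---|
| Outcome assessment | Outcomes only, by the listed criteria |
| Study outcomes | Criteria are death, critical illness, other serious infection, and new or persistent signs; no rash, diarrhoea or drug reaction |
| Follow-up | Receives adverse-event reports at home visits |
| Box 2 | Completes the SAE form |
| Adverse events | Documents the SAE and passes it on |

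The first row, read literally, cannot stand with the last three.

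**3. The 48-hour limit**

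- Gaps between assessor visits: 8 − 4 = 4 days, and 15 − 8 = 7 days.
- An event at home on day 9 that nobody reports until day 15 is learned of after 15 − 9 = 6 days, or 144 hours, against a limit of 48. This applies equally to an outpatient infant and a discharged inpatient infant.

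**4. Illustration (assumptions, not estimates)**

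Let the true adverse-event risk p be equal in both arms, inpatient detection complete, outpatient detection a fraction r, and n = 3500 per arm (Sample size).

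- Apparent outpatient risk: q = p × r.
- Apparent difference: q − p.
- Standard error: √[p(1 − p)/n + q(1 − q)/n].

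For p = 5% and r = 0.75: q = 3.75%, the difference is −1.25 points, and the standard error is √(0.05 × 0.95/3500 + 0.0375 × 0.9625/3500) = 0.49 points. The 95% interval half-width is 1.96 × 0.49 = 0.96 points. The chance of a spurious difference significant at two-sided 5% is 72%.

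The table shows the apparent difference in percentage points, with that chance in brackets.

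| True risk | r = 0.90 | r = 0.75 | r = 0.50 |
|---|---|---|---|
| 2% | −0.20 (9%) | −0.50 (36%) | −1.00 (93%) |
| 5% | −0.50 (16%) | −1.25 (72%) | −2.50 (above 99%) |
| 10% | −1.00 (30%) | −2.50 (96%) | −5.00 (above 99%) |

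The result is driven by r, about which the document says nothing.

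**The case against.** The strongest reply has four parts.

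1. **Outpatient events have several routes into the record.** Families may seek care at any time and may report to the assessor at home (Follow-up). Table 2 adds an assessor visit if the infant deteriorates and treatment-documentation contacts on days 2, 4 and 8. Patient safety adds staff phone numbers and counselling on signs of illness. This stands: outpatient recording is not confined to days 2 and 4. But care-seeking and volunteered reports favour noticeable or worrying events, and the documentation team has no stated adverse-event task. Mild, short-lived events remain exposed.
2. **The serious harms are protected.** Death, critical illness, other serious infection and new signs belong to the primary outcome, which assessors judge on the same days in both arms. SAEs share one assessor documentation route. This stands and limits the point to non-serious events, although notification of SAEs between visits could still differ by arm.
3. **The restriction on assessors may only mean that they apply fixed criteria and do not manage cases.** That is a reasonable reading, and it is why this is a contradiction to reconcile rather than proof that assessors ignore safety. The sentence as written still says something else.
4. **This is a condensed article, and Data analysis specifies no between-arm adverse-event comparison.** Checklists may well sit in the manual of operations or the case report forms, so their absence here is not the finding. What the article does state (the recorder, the contact schedule, the limit on assessors and the start of the clock) is what needs attention.

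A reader might go further and infer that outpatient care will look safer by design. The document does not support that. Daily ward observation is inferred, detection rates are unknown, and longer hospital exposure could cause genuinely more events. A reader might also infer that the 48-hour limit cannot be met for home events. That would require families to stay silent between visits despite the phone and care-seeking routes.

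**Conclusion.** The point holds as a risk of differential under-recording of non-serious adverse events in the outpatient arm during the treatment week. It rests on about 7 against 3 scheduled treating-staff days, with the inpatient figure inferred from the injection schedule, and on open-label recording. Its size cannot be estimated from the document. On assumed inputs the apparent difference runs from negligible to several percentage points, so no single value should be quoted as the expected bias.

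It does not extend to deaths or the primary outcome, nor to the period after discharge.

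Two wording faults stand beside it. The limit on assessors contradicts their safety tasks in Box 2, Follow-up and the adverse-events section. The 48-hour limit runs from occurrence, so it may be missed in either arm when a home event is learned of late. The overall weight is moderate: worth correcting because the trial intends to speak to safety and the correction is cheap.

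**What to change.** 1. In Outcome assessment and in the adverse-events section, state that the assessor asks the same short adverse-event checklist in both arms at the existing visits on days 2, 4, 8 and 15: diarrhoea, rash, drug reaction, injection-site problem, and any admission since the last visit. Reword the sentence limiting assessors to outcomes so that it agrees with Box 2 and Follow-up. If the manual of operations already contains such a checklist, the change reduces to this wording.
2. Base any between-arm comparison of adverse events on those visit records, and list treating-staff reports separately.
3. Start the 48-hour SAE reporting clock when staff become aware of the event, and record the date of occurrence as well, so that reporting delay can be seen.

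The cost is protocol and form wording plus a few minutes at visits that already take place, with no new staff or visits. The downside is that events seen only on the ward will appear only in the separate listing, so the compared rates will understate the total inpatient burden.
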